**Primary outcome**

The assessment of pain intensity in the episiotomy area and the evaluation of episiotomy wound healing

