2. Nahid Barati and Masoumeh Kordi (2020) conducted a clinical trial study titled the effect of black seed cream on episiotomy pain. This study was conducted on 124 primiparous women of Vali Asr Hospital in Birjand. The samples were randomly divided into three groups: black seed cream, placebo (cold cream) or routine care. Four hours after episiotomy, both placebo and black seed cream groups used the creams in the amount of 20 grams twice a day for 10 days. And the control group received usual care. Pain intensity was assessed before the intervention, 12 hours after the intervention, and on the seventh and tenth days after the intervention by the McGill questionnaire. There was no significant difference in the pain intensity in the three groups before the intervention and 12 hours after, but on the seventh and tenth days after the intervention, the pain intensity in the group receiving black seed cream was far less than the other two groups. The results of this study showed that black seed cream reduces the intensity of pain caused by episiotomy. Therefore, it can be used as a non-pharmacological method (16). This study examined the effectiveness of black seed cream only on pain intensity. However, the present study will investigate the effectiveness of the combination of black seed oil with olive oil on pain intensity and episiotomy wound healing.
3. M. Kaviani et al. (2017) conducted a study with the aim of determining the effect of olive leaf extract ointment on reducing the intensity of episiotomy pain and its recovery. This

---

 Redness, Edema, Ecchymosis, Drainage, Approximation

randomized trial was conducted on 90 women including three groups of 30 people who used olive leaf ointment, placebo and betadine solution three times a day for 10 days locally in the episiotomy area. Data were collected 4 hours after delivery and on the third, seventh, tenth and fourteenth days after delivery. Wound healing was evaluated by REEDA scale and pain intensity was evaluated by Visual Analog Pain Scale. The findings of the study showed that there was a significant difference between the olive leaf extract ointment group and other groups in terms of wound healing and pain. And this ointment is effective in reducing pain intensity and early complications of episiotomy (14).

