### Sample size

The sample volume was calculated at the confidence level of 95%, the power of the test was 80%, and according to the information of the article by Kurdi et al. (16) with values of  $\sigma_1=1.5$ ,  $\mu_1=5$ ,  $\sigma_2=2.2$ , and  $\mu_2=6.4$ , with the following formula and assuming dropout During the implementation, the number of 36 samples in each group is estimated.

$$n = \frac{(Z_{1-\alpha/2} + Z_{1-\beta})^2 (S_1^2 + S_2^2)}{(\mu_1 - \mu_2)^2}$$

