### Statistical analysis

The analysis method used in this study is intention-to-treat analysis, ensuring the maintenance of the random allocation process. After collecting the data in the first stage, the basic variables of the patients in the intervention and control groups will be compared to ensure the desirability of the random allocation process. SPSS version 20 software and ANOVA, chi-square, repeated measurements and multilevel mixed-effects linear regression will be used to analyze the primary results. For comparing pain intensity and episiotomy wound healing after the intervention in the 3 groups, the analysis of covariance (ANCOVA) test will be used, taking into account the measurements taken prior to the intervention. Multilevel linear regression will be conducted to adjust for confounding variables, including demographic, midwifery, and delivery-related factors. Additionally, the effect size will be demonstrated through mean differences and 95% CIs. A significance level of  $P < 0.05$  will be considered as the threshold for statistical significance

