The researcher will select and randomly assign the samples to two intervention groups and one routine care group according to the study entry criteria. Eligible people are placed in one of three groups A: 36 people, B: 36 people, and C: 36 people, using permuted block randomization and open label. 18 blocks of 6 will be produced to create a sequence of size 108. In order to keep the random allocation list secret, a special code will be assigned to each of the intervention groups, which only the main implementer of the project will be aware of. Also, the second moderator, who is a student and study evaluator, and the person who performs the statistical analysis, will not know about the codes assigned to the drugs. The intervention group consisted of two groups of mothers, one group will receive black seed and olive oil and the other group will receive olive oil alone. To prepare the product, cold-pressed black seed oil is used, as well as standard extra-virgin olive oil (according to the national standard). Standard extra virgin olive oil is prepared by a company with pharmaceutical grade (Pisgaman Chemi). Cold-pressed black seed oil is obtained from pharmaceutical company (Barij Essential Oil). Both oils are mixed in equal proportions and packaged (29). Both products have approved specifications in terms of microbial and pollution control standards, chemical and physical control. The process of mixing and packaging of two oils is done under hygienic conditions in the traditional pharmacy laboratory of the Faculty of Traditional Medicine. All study subjects will be educated on following post-delivery health tips and caring for episiotomy wounds. The intervention groups (one group receiving olive oil plus black seed oil and the other receiving olive oil alone) will also receive instructions on how to use the containers containing the oils. Women in the intervention groups will use the oils 24 hours after delivery, applying 10 drops topically 3 times a day for 10 days (12). The participants will be instructed to wash and dry their perineum before applying the oils. They should then wear gloves and slowly apply 10 drops of oil to the perineum, massaging it in with their hands. The control group will receive only routine care. The researcher also examines the severity of perineal pain and episiotomy wound healing in both groups, the first 24 hours after delivery and ten days after that. Given that each milliliter contains 15 drops, and mothers are required to use the oils 3 times a day, approximately 30 mL of each type of oil will be provided to mothers for the duration of 10 days. To measure the intensity of episiotomy pain, a 10-cm pain ruler scale (6, 12) will be used, the zero mark of which means no pain and the mark of 10 is the worst possible pain. Episiotomy wound healing will be assessed by the researcher using the Rida scale (6, 12, 17). In this way, the participant will be placed in a lithotomy position and the variables of redness, edema, ecchymosis, discharge and approximation between the two edges of the episiotomy wound will be scored based on the REEDA scale (12).

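### Pain and wound healing are unranked co-primary outcomes tested across three arms at one P < 0.05 threshold, and the 80% power describes only one unadjusted two-group contrast on pain

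*Protocol*

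**What the plan says.** The Primary outcome section names "The assessment of pain intensity in the episiotomy area and the evaluation of episiotomy wound healing". Neither comes first, and nothing says whether one or both must succeed.

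Under Data Collection and Management there are three arms, "A: 36 people, B: 36 people, and C: 36 people": combined oil, olive oil alone and routine care.

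The Statistical analysis section names ANCOVA "For comparing pain intensity and episiotomy wound healing after the intervention in the 3 groups". It promises mean differences with 95% confidence intervals and sets one significance threshold, P < 0.05. It names no main contrast, order of testing or adjustment.

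The Sample size section says that "the power of the test was 80"%, at 95% confidence. It uses a formula for two means with 5 (SD 1.5) and 6.4 (SD 2.2) from an earlier black seed cream trial, and arrives at 36 per group after an unstated dropout allowance. The Review of texts says of that trial: "This study examined the effectiveness of black seed cream only on pain intensity".

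**The concern.** Two co-equal primary outcomes, each tested at the full 5%, give two chances of a false primary claim. Three arms add further chances if pairwise differences are read as tests in their own right. With no order set in advance, whichever outcome or contrast turns out favourable can be presented as the primary result.

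The power statement names neither an outcome nor a contrast. Its formula and inputs fit one two-group comparison of pain. The introduction justifies the combination partly by what black seed oil adds to olive oil, so combination versus olive oil is of real interest, yet the sample size does not address it.

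**Working it through.** **Inputs.** From the Protocol: two-sided α = 0.05 (the formula uses Z at 1 − α/2), power 80%, means 5 and 6.4, SDs 1.5 and 2.2, three arms of 36, two primary outcomes. Assumed, because not stated: dropout rate, correlation between the outcomes, and the position of the olive oil arm.

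**1. The Protocol's own figure.**
n = (1.96 + 0.8416)² × (1.5² + 2.2²) / (5 − 6.4)² = 7.849 × 7.09 / 1.96 = 28.39, so 29 per group. With an assumed 20% dropout, 28.39 / 0.8 = 35.5, so 36. The stated size is thus reproduced as one unadjusted two-group comparison.

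**2. Power for that contrast.**
Power = Φ(1.4 / √(7.09/n) − z at 1 − α/2).

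| α | 29 per arm | 36 per arm |
|---|---|---|
| 0.05 | 80.8% | 88.4% |
| 0.025 (split over two outcomes) | 72.2% | 81.9% |
| 0.05/6 (split over six comparisons) | 57.7% | 69.7% |

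**3. False primary claims when no arm differs.**
Two independent tests at 0.05 give 1 − 0.95² = 9.75%. Three arms give three pairs, so two outcomes give six pairwise comparisons; six independent tests would give 1 − 0.95⁶ = 26.5%. Simulation allows for shared arms and correlated outcomes (20,000 trials, 29 per arm, normal data, no baseline adjustment):

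| Outcome correlation (assumed) | Pairwise tests only after a significant three-group test | Six ungated pairwise tests |
|---|---|---|
| 0 | 10.2% | 23.2% |
| 0.3 | 9.8% | 22.5% |
| 0.5 | 9.0% | 21.1% |
| 0.8 | 7.7% | 18.5% |

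**4. What the 80% does not describe.**
- *Three-group test on pain.* Assume means 5, 5.7 and 6.4 and common variance 7.09/2 = 3.545. The non-centrality is n × (0.7² + 0 + 0.7²) / 3.545, which is 8.02 at 29 per arm and 9.95 at 36. Power is 70.2% and 80.2%.
- *Combination versus olive oil on pain.* For an assumed 0.7-point difference, use the formula in step 2 with 0.7 in place of 1.4. With variance sum 7.09, power is 29.3% at 29 per arm and 35.1% at 36. With both SDs 1.5 (variance sum 4.5), it is 42.7% and 50.8%.
- *REEDA.* The Protocol gives no difference or SD, so no power can be computed.

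**The case against.** A reader might infer that the plan sets six primary tests, each at P < 0.05, with a false-claim rate above 20%. The Protocol does not support that as a statement of fact. The named test is a three-group ANCOVA, the hypotheses under Assumptions are mainly worded as three-group statements, and the mean differences are introduced as effect sizes. With three arms, pairwise tests made only after a significant three-group test hold the error near 5% within each outcome. The arms then add nothing, and the excess comes from having two outcomes. But the Protocol does not state that gate, so 18% to 23% stands as a worst case that it leaves open.

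A reader might also infer that the trial is badly underpowered. Figures at 29 per arm alone would suggest so, but 36 are randomised, and the three-group test then reaches 80% under the midway assumption. Baseline adjustment could help further: with an assumed baseline correlation of 0.5, that test would have about 83% even at 29 per arm. The power for combination versus olive oil rests on an assumed difference that the documents do not give.

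A multiplicity procedure may stand in a statistical analysis plan that is not shown. That could settle the error rate, provided the Protocol is made to agree. It could not change what the sample size was computed for.

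Finally, if both outcomes had to succeed, the error across outcomes would not be inflated, but joint power could not exceed the power for pain alone. The Protocol states no such rule.

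**Conclusion.** The point holds in a limited form and should be fixed. On the reading most favourable to the Protocol, the chance of at least one false primary claim is about 8% to 10%, up to twice the nominal 5%. This assumes an outcome correlation between 0.8 and 0 and no true difference on either outcome.

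The 80% power is arithmetically right for one unadjusted pain contrast of 1.4 points. The section does not say which two arms the means 5 and 6.4 represent, and the source trial had no combined-oil arm. Nor does it claim that the 80% covers REEDA or the second active contrast. The fault is that it leaves the scope unsaid in a three-arm trial with two primary outcomes.

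**What to change.** Before outcome data are seen:

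- **Statistical analysis.** Rank the primary outcomes and test them in a fixed order at two-sided 0.05: pain first, as the only outcome sized, and REEDA only if pain is significant. Within each outcome, either make pairwise comparisons only after a significant three-group test, or name one main contrast to be tested first (for example combination versus routine care). The three-group route protects the two overall claims. If pairwise results on both outcomes are also to count as confirmatory, they need places in the fixed order. The exact order is the sponsor's choice.
- **Sample size.** Say that 80% refers to a single pairwise pain contrast with a 1.4-point difference, and name the two arms. Add that REEDA and combination versus olive oil were not separately powered and are reported with 95% confidence intervals.
- **Study population and sampling method.** This section calls the trial a non-inferiority study, while the sample size and threshold are for testing differences. Reconcile the two before fixing the order.

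The cost is a paragraph in each of the first two sections and no added patients. REEDA cannot be claimed if pain fails, and the power statement becomes narrower. By comparison, keeping 80% power under a Bonferroni split over six comparisons would need 44 evaluable per arm. With an assumed 20% dropout that is 44 / 0.8 = 55 per arm, or 165 in total against the planned 108.

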**Secondary outcomes**

Burning and itching, as well as the occurrence of episiotomy opening and the need for painkillers

In this research, 3 questionnaires will be administered within the first 24 hours and 10 days after delivery.

**Data collection tools**

The data collection tool will be Demographic Characteristics Questionnaire, REEDA scale and Visual Analog Scale.

**Demographic Characteristics Questionnaire:** This questionnaire comprises 22 questions that gather information such as age, education level, place of residence, employment status, height, weight, number of pregnancies and abortions, duration of hospitalization during labor, receipt of antibiotics during labor and post-delivery, and hospitalization of the baby in the intensive care unit. The questionnaire was designed based on the research objectives to identify potential confounding variables.

**Visual Analog Scale for Measuring Episiotomy Pain Intensity:** The Visual Analog Scale, also known as the McGill Pain Ruler, is a linear scale used for pain assessment. It consists of a 10-cm ruler, with 0 indicating no pain and 10 indicating the most severe pain possible, and between these 2 endpoints, the scale is divided into 3 levels. Perineal pain intensity refers to the pain experienced by mothers in their perineal area and is self-reported before and after the intervention.

**The Redness, Edema, Ecchymosis, Discharge, and Approximation Scale:** The REEDA (Redness, Edema, Ecchymosis, Discharge, and Approximation) Scale is a standardized tool for assessing episiotomy wound healing, including variables such as swelling, bruising, discharge, redness, and the distance between the two edges of the episiotomy wound. Each of these variables is scored on a scale from 0 to 3. The researcher records the scores for each variable separately after observing and examining the patient both before and after the examination. The overall score on the scale ranges from 0 to 15, with higher scores indicating less favorable wound healing and lower scores indicating better wound healing.

**Secondary outcomes assessment checklist:** Secondary outcomes will be determined by a checklist that will be completed by mothers on a daily basis during the first ten days after delivery and will be examined by the researcher.

**Possible implementation problems**

Not using sterile tape and using eye examination.

Some mothers may not come for examination on the 10th day. (For example, due to hospitalization of the baby)

## Forecasting the timing of project implementation stages

| Stage length in months | Brief description of the selection process |
|------------------------|--------------------------------------------|
| 2 months               | Setting up the plan                        |
| 16 months              | Implementation steps of the plan           |
| 3 months               | Data analysis                              |
| 3 months               | Final project report                       |
|                        |                                            |

## Ethical considerations

- Necessary permission will be obtained from the research ethics committee of the honorable research vice president of the university in order not to contradict the study with research ethics.
- By obtaining a written letter of introduction from Babol University of Medical Sciences, the researcher will introduce himself to the relevant officials of the hospitals covered by the university.
- The researcher will clearly present his goals to the officials of the medical centers and the subjects of the research, verbally and in writing, and will get permission to conduct the research.
- Written consent will be obtained from the people participating in the research.
- Subjects will be free to agree or disagree to participate in the study or withdraw from it.
- All people participating in the research will be assured of the confidentiality of their information, and they can leave the study for any reason, such as choosing other methods of episiotomy wound care during the research.

